### Study design

Figure 1 shows an overview and the time course of the Baden-Württemberg Study.

**Figure 1 F1:**
[figure not shown]
**Overview and time course of the Baden-Württemberg Study**.

The Baden-Württemberg Study is a prospective, stratified, cluster-randomized, and longitudinal study consisting of an intervention group and a control group. The waiting control group design was realized in this study: in the academic year 2010/2011, the program's intervention was carried out in the intervention group whereas the control group followed the regular curriculum (without intervention). In the academic year 2011/2012, the control group started with the intervention, i.e. after one year time of waiting. Cluster-randomization was performed for participating primary schools in Baden-Württemberg. Blinding is not feasible in such a school based study. Measurements were performed at three different levels, namely level 1 "pupil", level 2 "parents", and level 3 "teacher and principal", see section "Data Collection". Participating children are 1^st ^grade and 2^nd ^grade pupils.

Measurements were taken at two points:

• First point: Baseline measurements were taken at the start of the academic year 2010/2011 in the period from mid September 2010 to mid November 2010 (i.e. from the end of summer vacation until the fall vacation in Baden-Württemberg in 2010)

• Second point: Follow-up measurements were taken at the start of the academic year 2011/2012 in the period from mid September 2011 to mid November 2011 (i.e. from the end of summer vacation until the fall vacation in Baden-Württemberg in 2011)

Pupils at randomized primary schools whose parents gave written consent for participation in the study were measured at the two points mentioned above.

Additionally, in November 2010 (baseline measurement) and November 2011 (follow-up measurement) a parental questionnaire was issued and returned within six weeks. Teachers and principals were also asked about characteristics of the school environment during follow-up.

A continuation of the Baden-Württemberg Study is planned as an observational study: pupils taking part in the study will be observed until they finish primary school.

### Actual status of study

At present (winter 2011), all follow-up measurements have been completed. In the next months, data management (scanning of case report form pages and verification of scanned data) and data checks will be performed before starting the statistical analyzes.

### Intervention

The intervention was developed by a team of scientists in collaboration with experienced primary school teachers and is developed for all levels of primary school (i.e. 1^st ^grade until 4^th ^grade). It combines elements from behavioral prevention and situational prevention. The three main goals of the intervention are to increase physical activity, to decrease the consumption of sugar-sweetened beverages, and to decrease time spent with screen media. The intervention follows a saluto-genetic, competence, and action oriented approach and is informed by Social Cognitive Theory [38]. The program's intervention is based on one academic year as part of lesson plans and recess. No additional physical education lessons are necessary to carry out the intervention but physical activity is integrated in the whole school day and in the school environment.

The intervention is implemented by the class teacher. For a progressive consolidation of the intervention's main goals from the 1^st ^grade until 4^th ^grade, a spiral curriculum is promoted: main topics are recessed from grade to grade. The intervention's rationale and contents are included in folders which contain the manual and materials for the intervention (1^st ^and 2^nd ^grade [39], 3^rd ^and 4^th ^grade [40]). Each class teacher belonging to the intervention group has taken part in a three-part local training course. The intervention itself includes 20 units per school year regarding the topics "beverages", "physical activities", and "recreational activities". These units are spread over the whole academic year. Furthermore, the intervention consists of two physical activity exercises which are performed every school day ("active breaks", each exercise takes between 5 and 7 minutes). Additionally, "family homework" exercises are given which are small tasks relating to the lesson's topics to involve the parents. Further, samples for parents' evenings and templates for letters to parents in three languages, i.e. German, Turkish and Russian, are included in the folder.

In the academic year 2010/2011, there was no intervention in the control group: although interested, the class teachers belonging to the control group received no local training and no materials for the intervention: they were registered for the participation in the academic year 2011/2012. In the academic year 2011/2012, these class teachers started with the three-part local training course (waiting control group design, see section "Study Design").

### Quality assurance and process evaluation

Process evaluation is ongoing to assess the quality of central training sessions for project delivery consultants and local training courses for school teachers. To further develop and improve the program, a process evaluation mainly using questionnaires, assessing implementation of and satisfaction with the given materials as well as structure and contents of the training courses is being carried out. Furthermore, information about work load when using the teaching materials and of the basic facilities of participating schools were gathered.

A scientific advisory board was established to support the research team and to help ensure the long-term quality of the program which meets regularly and reviews reports, study plans and results (see appendix).

### Data collection

The collection of data in the Baden-Württemberg Study is realized at three different levels:

• level 1 "pupil": measurement of anthropometric parameters, motor abilities, general well-being and body image was conducted in the total sample; computer-based test for attention and executive function as well as objective measurements of physical activity were performed in two subsamples because of organizational and technical reasons, see section "Study Sample".

• level 2 "parents": a self-constructed questionnaire for parents was used to measure parameters like socio-economic background, health behaviors and other related components.

• level 3 "teacher and principal": information about education and school environment was assessed.

### Assessments of the Baden-Württemberg Study

In the following section, details of all assessments used in the Baden-Württemberg Study are described. Measurements at level 1 "pupil" are characterized at first.

### Measurements at level 1 "pupil"

Measurements regarding the child's level are characterized in the following. All measurements were performed by four regional teams in fall 2010 and fall 2011 as described in section "Organization and Preparation of the Measurements". All measurements regarding the child's level were carried out in the classroom and gym of each primary school participating in the study.

#### Anthropometric Parameters

Measurements of the anthropometric parameters were performed according to the guidelines of the International Society for the Advancement of Kinanthropometry (ISAK). All examinations were performed by trained examiners in small groups of children separated by sex. Measurement of body weight was performed using calibrated flat scales (model 826, Seca^® ^Company, Germany). Mobile stadiometers (model 217, Seca^® ^Company, Germany) were used to measure body height. Waist circumference was measured halfway between the lower costal border and the iliac crest using a metal tape measure (Lufkin^® ^model W606PM, Lufkin Industries Inc., Texas, USA). Skinfold thickness was measured using calibrated Harpenden calipers (Baty International, Burgess Hill, UK) on the right hand side of the body. Triceps skinfold was measured halfway between the acromion border and the head of the radius on the back of the arm, subscapular skinfold was measured 2 cm down and out from the tip of the scapula.

#### Motor abilities

The Dordel-Koch-Test (DKT) [41,42] was performed by skilled examiners. The DKT is a test battery to assess the child's motor abilities including lateral jumps, sit and reach, standing long jump, sit-up, one-leg stand, push-ups, and a 6-min run.

#### General well-being and body image

General well-being was evaluated using an adapted Smilie-test [43] and body image was evaluated using the Figure Rating Scale [44] during a 1:1 interview, performed by trained examiners.

#### Mental abilities

Assessment of mental abilities was done using a computer-based test battery for attention and executive function (KiTAP) [45]. Three tasks from the KiTAP were used to assess the following mental abilities in the Baden-Württemberg Study: inhibition control, sustained attention, and mental flexibility. Number of errors and response time were measured for each task. The tests were performed by trained examiners in small groups using laptops with equivalent screen sizes. Each examiner tested 1 or 2 children at a time. Mental abilities were investigated in a subsample of the Baden-Württemberg Study.

#### Objective measurements of physical activity using accelerometry

Objective measurements of physical activity were performed using the Actiheart^® ^activity sensor (CamNtech, Cambridge, UK; The Actiheart User Manual 4.0.35. http://www.camntech.com/index.php). Activity sensors were worn continuously over a period of at least four to six successive days (two weekend days and two to four weekdays were included). Heart rate (beats per minute) and bodily acceleration (counts per minute) were recorded at 15 second intervals. Objective measurements of physical activity were performed in a subsample of the Baden-Württemberg Study.

### Measurements at level 2 "parents"

In the following section, details of all measurements on the parental level are described. The variables were assessed using a parental questionnaire.

#### Health-related quality of life

Health-related quality of life was assessed using two different instruments: the KINDL^®^-questionnaire (KINDL^® ^Manual [46]) and a visual analogue scale. Concerning the KINDL^® ^the 24 item-version for external assessment (in German) was used. Health-related quality of life was also assessed using the visual analogue scale (VAS) of the EQ-5D-Y questionnaire [47]. A proxy - version was used in the Baden-Württemberg Study: parents had to assess the child's health-related quality of life from their child's perspective.

#### Emotional fitness

Emotional fitness was assessed using the Children's Behaviour Questionnaire (CBQ) [48]. In the long version the CBQ includes 195 items assessing 15 scales. The short version of the CBQ includes 94 items assessing the same scales. For the Baden-Württemberg Study a selection of 55 items from the short version assessing 9 scales was made: activity level, impulsivity, anger/frustration, fear, sadness, soothability, smiling and laughter, attentional focusing, inhibitory control.

#### Socio-demographic variables

The following socio-demographic variables were asked in the parental questionnaire: the child's sex and date of birth, household income, size of flat, number of persons living in the household, number of working hours, employment status, educational level, and level of parents' professional training.

#### Further variables

Further variables asked in the parental questionnaire are, for instance, the variables for the child's anamnesis, risk factors for development of childhood overweight, child's behavior regarding nutrition, physical activity, and electronic media usage, as well as parental behavior regarding nutrition, physical activity, and electronic media usage and parents' attitudes to health.

### Measurements at level 3 "teacher and principal"

In the following, details of all measurements regarding the level "teacher and principal" are described. These measurements were carried out at follow-up only.

Two different questionnaires for intervention group and control group were used: in both study groups, characteristics of each school were collected about the number of pupils and teachers, the number of pupils with migration background, the concept of the school (e.g. full-time school, school with mixed-grades), recess format, school building and school environment (e.g. safety of way to school, form of settlement).

### Organization and preparation of the measurements

Pre-tests were performed to practice the planned procedure of the assessments. At first, in spring 2010 pre-tests for the different measurements at the level "pupil" were performed in several primary schools and kindergartens (final year) to ensure the practicability and feasibility of the assessment tools in children just entered school. For training purposes further preliminary tests in primary schools were carried out by each regional team before starting baseline measurements in fall 2010 and before starting follow-up measurements in fall 2011. Further, three different versions of the parental questionnaire were tested in May 2010 and June 2010 at five primary schools. None of these mentioned schools were later involved in the study.

Data collection at the level of pupils was conducted from the end of the summer vacation until the beginning of the fall vacation in 2010 and in 2011, respectively. For practical reasons four regional teams were established for data collection. Each team consisted of about 10 persons (two scientists and about 8 trained student assistants). The scientists are members of the research group in Ulm, the student assistants were recruited in the respective region. The scientists were trained in measuring anthropometric parameters by external experts. In addition; they were trained in handling and using Actiheart^® ^activity sensors. Student assistants were trained by the scientists in performing the DKT, interviews, computer-based test with children, and collecting anthropometric data with the exception of skinfolds. Skinfold thickness was only measured by scientists of the research group. Each team was measuring pupils of one or two classes per day; however, each school was measured separately.

The parental questionnaires were issued in November 2010 and November 2011, respectively, and returned within six weeks. Teachers and principals completed questionnaires at the second time in fall 2011.

### Recruitment process and randomization process

Information about the program and Baden-Württemberg Study were issued during the academic year 2009/2010 using a number of ways, e.g. education and health authorities, and universities of education; electronic newsletter; television and radio; adverts in training catalogs for primary school teachers; participation at trade shows. The recruitment process was also promoted by ten informative events in different parts of Baden-Württemberg. Further, all primary schools of the state of Baden-Württemberg received written information about the program and the structure of the study, asking teachers to participate. Interested teachers contacted the program center. The participation in the program was voluntary, participating teachers had to agree with randomization. In total, written consent from 172 primary school teachers and principals at 94 schools was obtained (see Figure 2). Teachers who already took part in the program in the academic year 2009/2010 were not included in the study. Because the grade level (1^st ^grade vs. 2^nd ^grade) may play a key role for the efficacy assessment, stratification of randomization was carried out for grade level according to the following procedure. Based on information about the distribution of the 172 teachers within the 94 schools, stratification according to number of classes and grade level (grade) was realized for the randomization process: six different school types were identified and used as strata for randomization:

• Primary schools with only one class (only one 1^st ^grade)

• Primary schools with only one class (only one 2^nd ^grade)

• Primary schools with more than one class (only 1^st ^grades)

• Primary schools with more than one class (only 2^nd ^grades)

• Primary schools with more than one class (1^st ^grades and 2^nd ^grades)

• Primary schools with mixed-grade classes (i.e. classes with pupils from 1^st ^and 2^nd ^grade)

There were 8 teachers at 3 schools who withdrew consent before randomization because of unknown reasons. Thus, randomization was performed for 164 teachers within 91 schools intervention group (IG): n = 45 schools, control group (CG): n = 46 schools). Written consent was withdrawn from 7 teachers within 5 schools immediately after randomization (IG: n = 1 school (reason: too much effort), CG: n = 4 schools (reason: randomization in control group)). Therefore, 86 schools (IG: n = 44 schools (n = 81 classes), CG: n = 42 schools (n = 76 classes)) were included in the Baden-Württemberg Study at baseline. The result of the stratified randomization was the following distribution of classes within both study groups:

• Intervention group: 1^st ^grade classes: n = 39, 2^nd ^grade classes: n = 32, mixed-grade classes: n = 10

• Control group: 1^st ^grade classes: n = 36, 2^nd ^grade classes: n = 29, mixed-grade classes: n = 11

Baseline measurements were conducted in 157 classes (i.e. 157 primary school teachers were included). One teacher at a school randomized in a 1^st ^grade class in the control group withdrew the consent shortly before follow-up (reason: parents' request). However, that school remains in the Baden-Württemberg Study because another class at that school took further part in the measurements at follow-up. Another two teachers randomized in a 1^st ^grade class in the control and intervention group, respectively withdrew consent at follow-up (reasons: school building burnt down and unknown). Thus, at follow-up the distribution of classes within both study groups was as follows:

• Intervention group: 1^st ^grade classes: n = 38, 2^nd ^grade classes: n = 32, mixed-grade classes: n = 10

• Control group: 1^st ^grade classes: n = 34, 2^nd ^grade classes: n = 29, mixed-grade classes: n = 11

In total, follow-up measurements were taken in 154 classes within 84 schools.

### Study sample at baseline

In total, 3159 pupils were in the participating classes and 1968 parents (62.3%) of pupils at primary schools participating in the Baden-Württemberg Study gave written informed consent to participate.

Baseline measurements (fall 2010) were taken from 1947 children and data at all three levels ("teacher and principal", "parents", and "pupil") was available from 1670 children (IG: n = 916 (54.9%), boys: n = 452 (49.3%); CG: n = 754 (45.1%), boys: n = 388 (51.5%)). The distribution of these pupils within each grade is shown in Table 1:

**Table 1 T1:** Baseline measurement: Distribution of pupils of which data at all three levels are available (IG: intervention group, CG: control group)

grade	group	n (%)	% of boys
**1**	IG	411 (53.4%)	50.1%
	
	CG	358 (46.6%)	50.6%

**2**	IG	382 (55.5%)	45.6%
	
	CG	306 (44.5%)	50.3%

**mixed-grade classes (1/2)**	IG	123 (57.7%)	58.5%
	
	CG	90 (42.3%)	58.9%

The computer-based test for attention and executive function (KiTAP) were performed in a subsample of 513 pupils belonging to 45 classes within 27 schools (IG: 54.8%; boys: 50.3%), objective measurements of physical activity using Actiheart^® ^were performed in 384 pupils belonging to 56 classes within 32 schools (IG: 55.2%; boys: 50.3%). Results of baseline measurements in both subsamples are presented elsewhere [49,50].

Figure 2 shows the flow chart of enrollment, baseline measurements, and follow-up in the Baden-Württemberg Study.

**Figure 2 F2:**
[figure not shown]
**Flow chart of enrollment, baseline measurements, and follow-up in the Baden-Württemberg Study**.

### Power considerations

Power calculations were made at beginning of the study based on the availability of data for the main outcome parameters at baseline. Three main outcome parameters for the assessment of efficacy are specified in the study protocol: change in waist circumference, change in subscapular skinfold thickness and change in 6-min run performance, changes are calculated as differences between follow-up measurement and baseline measurement. All power calculations are based on simulations of hypothetic data and application of linear mixed effects models [51,52]. An adjustment according to Bonferroni was made to account for multiple testing [53]. In each mixed effects regression model only group (intervention group vs. control group) was used as explanatory variable and no distinction was made between several classes within the same school. Data from the project URMEL-ICE were used for specifying the differences between intervention group and control group. Randomization data were used for specifying the numbers of schools: IG: n = 44 schools, CG: n = 42 schools. Numbers of baseline measurements available for each primary outcome were used for calculation of pupil numbers in each study group:

• waist circumference: n = 1893 (IG: n = 1038, CG: n = 855)

• subscapular skinfold thickness: n = 1855 (IG: n = 1014, CG: n = 841)

• change in 6-min run performance: n = 1884 (IG: n = 1034, CG: n = 850)

Using this information, the following assumptions were made for the number of pupils in each school:

• change in waist circumference: IG: n = 24 (~1038 pupils in 44 schools); CG: n = 20 (about 855 pupils in 42 schools)

• change in subscapular skinfold thickness: IG: n = 23 (~1014 pupils in 44 schools); CG: n = 20 (about 841 pupils in 42 schools)

• change in 6-min run performance: IG: n = 24 (~1034 pupils in 44 schools); CG: n = 20 (about 850 pupils in 42 schools)

Furthermore, it was assumed that a percentage of 80% measurements available at baseline will be available at the follow-up, too. This percentage is an approximate value and was observed in the project URMEL-ICE.

The simulation results showed that the following values for statistical power could be reached if the assumptions proved right: 85% (change in waist circumference), 76% (change in subscapular skinfold thickness), and 74% (change in 6-min run performance).

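### Bonferroni is the only multiplicity rule given for the three main outcomes; Holm's step-down would keep the same error control and never reject less

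*Protocol article*

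**What the plan says.** All of the relevant text is in *Power considerations* of the protocol article.

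- Number of outcomes: "Three main outcome parameters for the assessment of efficacy are specified in the study protocol". They are the changes in waist circumference, subscapular skinfold thickness and 6-minute run performance.
- Multiplicity: "An adjustment according to Bonferroni was made to account for multiple testing". The sentence is in the past tense and belongs to the description of the power simulations.
- Effects: "Data from the project URMEL-ICE were used for specifying the differences between intervention group and control group". No differences, standard deviations, intraclass correlations, alpha or sidedness are printed.
- Result, conditional on the assumptions being right: "85% (change in waist circumference), 76% (change in subscapular skinfold thickness), and 74% (change in 6-min run performance").

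*Statistical considerations* offers mixed models or GEE as examples for the final analysis and is silent on multiplicity. The Abstract calls the power sufficient and the Discussion calls it adequate. *Actual status of study* says that follow-up measurement is complete and that statistical analysis has not begun.

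**The concern.** Bonferroni holds every one of three tests to a third of the familywise alpha, even after another outcome has already been rejected. Holm starts at the same threshold but relaxes it to alpha/2 after the first rejection and to alpha after the second. Its error guarantee is the same and needs no assumption about how the outcomes are correlated. When several effects are expected, as the simulation assumes here, the difference is not trivial.

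At 76% and 74%, a true effect of the assumed size would be missed about one time in four on each of two main outcomes, and part of that loss comes from the testing rule. The sample can no longer grow. The testing rule is one of the few things that can still be improved without having seen results.

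**Working it through.** **Inputs.** From *Power considerations*: three outcomes, Bonferroni, powers of 0.85, 0.76 and 0.74. Assumed because the article gives no figure: familywise alpha 0.05 two-sided, normal test statistics, and the correlations between them.

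**Step 1: back-solve the effects.** The powers cannot be rebuilt from first principles, so each is inverted to a mean z value:

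mean = z(1 − 0.05/6) + z(power), with z(1 − 0.05/6) = 2.394

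- Waist: 2.394 + 1.036 = 3.430
- Skinfold: 2.394 + 0.706 = 3.100
- Run: 2.394 + 0.643 = 3.037

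Bonferroni then returns 85/76/74% by construction. That is a consistency check and not an independent reproduction.

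**Step 2: power at each Holm threshold**, Φ(mean − critical value):

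| Threshold | Waist | Skinfold | Run |
|---|---|---|---|
| alpha/3 (A) | 0.850 | 0.760 | 0.740 |
| alpha/2 (B) | 0.883 | 0.805 | 0.787 |
| alpha (C) | 0.929 | 0.873 | 0.859 |

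**Step 3: Holm power with independent statistics, all three effects real.** For outcome i with the others j and k:

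A_i + (B_i − A_i)[1 − (1 − A_j)(1 − A_k)] + (C_i − B_i)[B_j B_k − (B_j − A_j)(B_k − A_k)]

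Skinfold: 0.760 + 0.0448 × (1 − 0.15 × 0.26) + 0.0681 × (0.8828 × 0.7870 − 0.0328 × 0.0470) = 0.760 + 0.0430 + 0.0472 = 0.850.

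The same formula gives 0.910 for waist and 0.837 for run. Simulation agrees to within 0.1 percentage point.

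**Step 4: correlated statistics, by simulation.** Correlations are listed as waist-skinfold / waist-run / skinfold-run and are assumptions.

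| Correlation | Holm: waist / skinfold / run | All three rejected: Bonferroni to Holm |
|---|---|---|
| 0 / 0 / 0 | 91 / 85 / 84% | 48% to 69% |
| 0.5 / 0.2 / 0.2 | 90 / 84 / 83% | 54% to 72% |
| 0.7 / 0.4 / 0.4 | 89 / 84 / 83% | 58% to 74% |
| 0.99 throughout | 85 / 81 / 81% | 73% to 81% |

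The independent Bonferroni figure for all three is 0.85 × 0.76 × 0.74 = 0.478.

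**Step 5: when some effects are absent (independent statistics).** Suppose waist has no effect. The skinfold test then gets the alpha/2 threshold mainly when run is rejected first: 0.760 + 0.0448 × 0.74 = 0.793. Chance rejections of waist bring the simulated value to 79.4%. All simulated values:

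| No effect in | Skinfold | Run |
|---|---|---|
| Waist | 79.4% | 77.7% |
| Skinfold | – | 78.1% |
| Run | 79.9% | – |
| Both other outcomes | 76.2% | 74.1% |

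**Step 6: robustness.**

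- With independent statistics, a one-sided alpha of 0.05 gives 85.9% and 84.6% for skinfold and run; a one-sided alpha of 0.025 gives 85.0% and 83.7%.
- If the stated powers are at the low end of rounding (84.5/75.5/73.5%), Holm still gives 81.6% and 80.9% for skinfold and run at a correlation of 0.9.
- The simulated familywise error of Holm with no effect anywhere and independent tests is 4.9%.

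**The case against.** The strongest objection is that the article does not say the final tests will use plain Bonferroni. The sentence describes the simulation, the analysis section is silent, and the full analysis plan is not shown and may name another rule. Power quoted under Bonferroni is also a safe lower bound for a later Holm analysis. This stands. A reader might infer that the outcomes are fixed to be tested at 0.05/3 each, but neither the rule for the final tests nor the alpha is stated. What can be said is that Bonferroni is the only rule given and the one under which power is reported.

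A second objection is that the gain is conditional. This stands too. A reader might infer that Holm simply lifts skinfold and run above 80%, but Step 5 shows that this needs all three effects to be real. All three are assumed in the simulation, yet the Background reports only tendencies for the two body-fat measures in the precursor project, and the Discussion concedes that one academic year may be too short and that contamination lowers power.

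Third, the document sets no 80% target and does not require success on all three outcomes, so calling two outcomes under-powered applies an outside convention. Finally, Bonferroni is valid and gives simpler simultaneous intervals. Both points are fair. They limit the weight of the finding but leave intact that Holm never rejects less at the same error level.

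**Conclusion.** The point holds as a free improvement in efficiency. It is not an error in type I control, and nothing in the article is wrong or contradictory here.

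Holm dominates Bonferroni without any assumption. The size of the gain does rest on assumptions: two-sided familywise alpha 0.05, effects back-solved from the stated powers, and correlations that the article does not give. On those terms, with all three effects real, the gain is about 4 to 6 percentage points for waist, 8 to 9 for skinfold and 9 to 10 for run, from independence to the moderate correlations. With one null outcome it shrinks to about 3 to 4 points for skinfold and run, and with two it almost vanishes. Power is never lower than under Bonferroni.

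**What to change.** Before the statistical analysis starts, state that the three main-outcome p-values are tested by Holm's procedure: the smallest at alpha/3, the next at alpha/2 and the largest at alpha, stopping at the first non-rejection. State alpha and sidedness, and that a separate claim is made for each rejected outcome. If the unseen analysis plan already says this, nothing more is needed there.

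For power, either keep 85/76/74% and label them as a lower bound under Bonferroni, or requote them under Holm and say that the figures require all three assumed effects to be real.

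The cost is a sentence or two of wording and, if power is requoted, one rerun of the existing simulation. No data or design change is needed. The one small downside is that simultaneous confidence intervals matching Holm are less simple than Bonferroni intervals.
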